### Composite reference standards

An assumption of standard diagnostic accuracy studies is that the reference standard is infallible. This constrains the performance of the index test to the performance of the reference standard and assumes every time the tests get different results the reference is correct and the index is incorrect. There is evidence of substantial heterogeneity of diagnostic accuracy of SARS-CoV-2 d/rRT-PCR testing, with reported false negative rates of 18–58% [36]. Both clinical context and repeated testing are highly relevant to calculating the likelihood of true negative cases [37], and so we will undertake further analyses using the composite reference standard.

Composite reference standard 1 will be designed to minimise false negatives (FNs), and composite reference standard 2 will be designed minimise false positives (FPs). Both composite reference standards will be constructed considering paired antibody test results, patient reported outcomes, linked EHRs for outcomes related to COVID-19, such as hospitalisation or death, other test results (Table 4).

**Table 4 Tab4:** Potential use of tests to enhance the reference standard. Information in the table refers to hypothetical combinations of results in which the enhanced reference standard result would be considered different from the original reference standard result. A cell-by-cell interpretation of each scenario follows.

	Minimise FN for current infection		Minimise FN for past infection	
Visit (day)	1 (0)	2 (28)	1 (0)	2 (28)
**SARS-CoV-2 RT-PCR**	Negative (FN)	N/A	Negative	N/A
**COVID IgG**	Negative	Positive	Negative (FN)	Positive
Or:	Subsequent positive SARS-Cov-2 RT-PCR result (within 28 days)		-	
Or:	Hospital admission or death (within 28 days) citing SARS-CoV-2 as probable cause		Hospital admission or death (within 28 days) citing SARS-CoV-2 as probable cause	
	**Minimise FP for current infection**		**Minimise FP for past infection**	
**Visit (day)**	1 (day 0)	2 (28)	1 (day 0)	2 (28)
**SARS-CoV-2 RT-PCR**	Positive (FP)	N/A	Negative	N/A
1.1.35. **COVID IgG**	Negative	Negative	Positive (FP)	Negative
And:	No subsequent positive SARS-Cov-2 RT-PCR result (within 28 days)		-	
And:	No hospital admission or death (within 28 days) citing SARS-CoV-2 as probable cause		No hospital admission or death (within 28 days) citing SARS-CoV-2 as probable cause	

Minimise FN (false negative) for current infection: If the COVID-19 RT-PCR reference test gives a negative result, it can be considered a false negative if the IgG result is positive at 28 days (newly positive or titres have increased), OR if a subsequent SARS-Cov-2 RT-PCR result (within 28 days) was observed, OR if there was a hospital admission or death (within 28 days) citing SARS-CoV-2 as probable cause

Minimise FP (false positive) for current infection: If the COVID-19 RT-PCR reference test gives a positive result, it can be considered a false positive if the IgG result is negative at both baseline and 28 days, AND if no subsequent SARS-Cov-2 RT-PCR result (within 28 days) was observed, AND if there was no hospital admission or death (within 28 days) citing SARS-CoV-2 as probable cause

Minimise FN (false negative) for past infection: If the baseline reference IgG test result is negative, it can be considered a false negative if the 28-day IgG test result is positive, OR if there was a hospital admission or death (within 28 days) citing SARS-CoV-2 as probable cause

Minimise FP (false positive) for past infection: If the baseline reference IgG test result is positive, it can be considered a false positive if all other tests at baseline and at 28 days are negative, AND there has been no hospital admission or death (within 28 days) citing SARS-CoV-2 as probable cause

Paired antibody testing at 0 and 4 weeks will identify changes in antibody levels over time. These serial laboratory samples will allow us to identify antibody changes to discriminate between current and past infection, and to highlight possible FP and FN RT-PCRs, whilst it remains possible that infection could occur after the index test but prior to the day 28 serology sample, this is unlikely to be a frequent event.

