### Setting

RAPTOR-C19 sites will be community based. The primary community setting will be primary care, focussing on general practices reviewing patients with suspected COVID-19 or acting as COVID-19 hubs. Practices that have submitted an expression of interest to take part in the study will be selected with the help of the National Institute for Health Research (NIHR) Clinical Research Network (CRN). RAPTOR-C19 sites will be reimbursed per patient recruited for their participation in the research. Participants will not be paid for their participation in the research.

Practices will be initially recruited through Oxford Royal College of General Practitioners (RCGP) Clinical Informatics Digital Hub (ORCHID) [30]. The surveillance platform of ORCHID is called the Oxford-RCGP Research and Surveillance Centre (RSC). General practices within this network are experienced in taking virology samples and serology specimens and have adapted their long established influenza surveillance to provide a sentinel system for COVID-19, including sero-surveillance [31]. Additionally, they have also previously successfully integrated POCTs into primary care clinical workflow in the 2018/2019 flu season [32, 33] with an additional pilot conducted across the 2019/2020 season. Recruiting patients into RAPTOR-C19 is an integral part of the planned 2020/21 ORCHID/PHE surveillance [34]. Patients who volunteer to provide samples for surveillance will have the opportunity to take part in RAPTOR-C19 in participating practices, and samples taken, with consent through RAPTOR-C19, will also be available to use for national surveillance.

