#### Reference laboratory tests

The current PHE reference standard for active infection is an OP/NP swab for laboratory real-time RT-PCR triplex assay for the detection of SARS-CoV-2. It incorporates multiplex detection of two SARS-CoV-2 targets (Orf1ab and E genes) and uses a soil borne cereal mosaic virus internal control [35]. It is important to note that reference laboratory tests for current infection will be done as part of clinical care or as part of the national surveillance system. Individuals can have these done whether or not they agree to be part of research.

Only adult participants (≥16 years old) will be asked to submit a blood sample for antibody testing for use as the reference standard for past SARS-CoV-2 infection and within the composite reference standard (see below) for current infection. Adults will have blood samples for this drawn at baseline and follow-up visits by appropriately trained staff.

Participants will receive clear instructions on how to sample, as per PHE standard advice. If participants are unable to self-swab, or express a preference, a staff member with appropriate training will take the sample. The sample material will fall under PHE or other central testing laboratory and not our study remit, and under current rules PHE may retain the swab for up to 5 years. Participants will be able to discuss the results of the PHE reference standards with their GP.

Once taken, the samples will be put in the regulation container packaging, double bagged, and sent to the PHE laboratory or other central testing centre laboratory that is supporting the study using their existing, safe, quality compliant processes. Participants will have the option to agree to this sample being retained for future surveillance or research use.

We acknowledge that the PHE reference standard and the details of the assay may change throughout the study as more accurate reference tests are adopted. POCTs will always be benchmarked against the current best practice. We will report the reference standard tests used in each POCT evaluation when each evaluation is submitted for publication. We will also compare POCTs to any change reference standards to mitigate the imperfect reference tests, and adjust our statistical analysis to reflect these potential changes.

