### Subsequent visits

Where feasible, adult (≥ 16) participants will also be invited to attend a second visit, or visited at home by a research nurse, 28 days following the first visit, to allow for a blood test for repeat antibody testing as outlined above.

Adult participants may be contacted by text message to complete an online daily symptom diary prior to the follow-up visit.

The time schedule of enrolment, assessments, and visits for participants is summarised in Table 2.

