### Stopping criteria

Assuming a test with 90% sensitivity, a 99% specificity, and a pre-test probability (prevalence) of 30%, we would require 200 participants to meet the minimum thresholds as stated above. This would also mean that tests with more than seven false negatives or two false positives could be immediately dropped from the study. This allows us to exclude tests with sensitivities of 50%, 60%, 70%, or 80% after the first 50, 60, 80, and 120 participants recruited. For tests with poor specificities of 80%, 85%, 90%, or 95% these would be identified after 15, 20, 30, and 60 participants recruited. The prevalence of COVID-19 affects the sample size required. With a pre-test probability (prevalence) of 5% we would require 1200 participants to evaluate a POCT and interim futility analyses will stop the evaluation after seven false negatives or twelve false positives. POCTs with an actual sensitivity of 50%, 60%, 70%, or 80% would reach futility criteria after the first 280, 350, 470, and 700 participants. POCTs with an actual specificity of 80%, 85%, 90% or 95% would reach futility criteria after the first 65, 85, 130, and 255 recruited participants.

Evaluations of the first POCTs will be performed without implementation of stopping criteria to establish whether sufficient information to create the composite reference standard can be obtained sufficiently quickly to make these criteria viable. The figures presented here should therefore be regarded as indicative for a POCT designed to detect active infection and will be reviewed once this information becomes available.

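### Day-28 IgG alone can turn an RT-PCR-negative adult into a missed infection with no exception for vaccine antibody, which could bias enhanced sensitivity downwards, most at low prevalence

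*Protocol article*

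**What the plan says.** Under Composite reference standards, Table 4 and the text that interprets it set out when the enhanced reference result may differ from the laboratory result. For current infection, a negative RT-PCR can be overturned by antibody: "it can be considered a false negative if the IgG result is positive at 28 days (newly positive or titres have increased"). For past infection, a negative baseline IgG can be overturned in the same way: "it can be considered a false negative if the 28-day IgG test result is positive". In both rules the antibody criterion is joined to the others by OR, so it is enough by itself.

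The same section names one competing explanation for seroconversion, infection between the visits, and expects it to be rare. The sentence, cut short here, reads: "it remains possible that infection could occur after the index test but prior to the day 28 serology sample, this is unlikely to be a". Vaccination is not mentioned there, in the eligibility criteria of Table 1, or elsewhere in the article. The antigen that the laboratory IgG assay detects is not stated either.

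Antibody also defines the standard reference for past infection. Under Reference laboratory tests, adults "will be asked to submit a blood sample for antibody testing for use as the reference standard for past SARS-CoV-2 infection". The paired sample comes from a second visit, offered to adults where feasible, "28 days following the first visit, to allow for a blood test for repeat antibody testing".

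The subsection on summary statistics of diagnostic accuracy bases the enhanced 2×2 tables for active infection on the composite standards of Table 4.

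**The concern.** The target condition is symptomatic COVID-19, active or past. A new or rising IgG supports that diagnosis only if infection is the sole likely source of the antibody. Vaccination is another possible source, and it differs from the one the article discusses, because no infection occurs at all.

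An uninfected adult with a negative RT-PCR and a correct negative POCT, vaccinated between visits, could be moved into the infected column of composite standard 1. The correct POCT result then counts as a false negative. At low prevalence the uninfected far outnumber the infected, so a small relabelled share of a large group can rival the number of real infections.

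For antibody POCTs, an adult vaccinated before baseline could be reference-positive for past infection without ever having been infected. The reference would then measure antibody from any source. That part is not quantified here.

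**Working it through.** **Inputs from the article.** The Stopping criteria section gives the high-prevalence case: "Assuming a test with 90% sensitivity, a 99% specificity, and a pre-test probability (prevalence) of 30%, we would require 200 participants". Its low-prevalence case is 5% prevalence with 1200 participants and a limit of seven false negatives. The minimum acceptable sensitivity, under Number of participants, is 80%.

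**Input that is assumed.** Let v be the share of all RT-PCR negatives who are uninfected but relabelled because of vaccine IgG. It is the product of three shares: those with a day-28 sample, those vaccinated at a time that produces a new or rising IgG, and those in whom the assay detects it. The documents give none of these shares for vaccination, so v is varied from 0 upwards.

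**Reproducing the plan's own figures.** Participants needed to reach seven false negatives at 5% prevalence = 7 / [0.05 × (1 − Se)]. For Se = 50%, 60%, 70% and 80% this gives 280, 350, 467 and 700, against the stated 280, 350, 470 and 700. The inputs are therefore read as the article uses them.

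**Effect of relabelling, RT-PCR treated as perfect.** Let P be the true infections, all RT-PCR positive, and R = v × (RT-PCR negatives). The POCT is positive in 90% of P and in 1% of R, so

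enhanced sensitivity = (0.90P + 0.01R) / (P + R).

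Both scenarios have P = 60 (5% of 1200; 30% of 200). RT-PCR negatives number 1140 and 140.

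| v | 5% prevalence: R | Sensitivity | 30% prevalence: R | Sensitivity |
|---|---|---|---|---|
| 0 | 0 | 54/60 = 90% | 0 | 90% |
| 1% | 11.4 | 54.114/71.4 = 75.8% | 1.4 | 54.014/61.4 = 88.0% |
| 5% | 57 | 54.57/117 = 46.6% | 7 | 54.07/67 = 80.7% |
| 20% | 228 | 56.28/288 = 19.5% | 28 | 54.28/88 = 61.7% |

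**Share needed to fall below 80%.** Setting the formula equal to 0.80 at prevalence p gives v = 0.10p / [0.79(1 − p)]. This is 0.67% at 5% prevalence and 5.4% at 30%.

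**Specificity.** The relabelled participants leave the uninfected group with the same 1% POCT positivity as those who stay, so specificity remains about 99%.

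**Allowing for imperfect RT-PCR.** The article cites RT-PCR false-negative rates of 18% to 58%. Suppose the 60 are the RT-PCR positives, composite 1 recovers every missed infection, and the POCT is still 90% sensitive in those cases. True infections are then 60/0.82 = 73 to 60/0.42 = 143, and the uninfected number about 1127 to 1057. Applying v to the uninfected:

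- v = 1%: (65.85 + 0.11)/(73.17 + 11.27) = 78% to (128.57 + 0.11)/(142.86 + 10.57) = 84%.
- v = 5%: (65.85 + 0.56)/(73.17 + 56.34) = 51% to (128.57 + 0.53)/(142.86 + 52.86) = 66%.

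The bias keeps its direction but is smaller.

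**The case against.** The strongest reply is that the problem depends on facts the article does not contain: a vaccine in use during recruitment, doses given at the relevant time, and an assay that detects the resulting antibody. The nearest statement on timing is that recruitment is an "integral part of the planned 2020/21 ORCHID/PHE surveillance", which says nothing about vaccination. This stands. The size is conditional, no value of v has support in the documents, and 20% is purely illustrative.

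The rules are also tentative. The text says a result can be considered false, and the table is headed as potential use: "Information in the table refers to hypothetical combinations of results in which the enhanced reference standard result would be considered different". The SAP and the list of captured data items in the supplement are not shown, and the article expects amendments and changes of reference test. A reader might infer that every new or rising IgG is taken as proof of infection, or that vaccination goes unrecorded. The documents support neither. What remains is that the enhanced active-infection tables are tied to Table 4, and that the article itself weighs rival causes of seroconversion and names only one.

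The scope is limited too. The harm quantified here falls on a secondary objective, under one of two composites, in adults with a day-28 sample; children give no blood and the second visit is optional. These limits are already inside v, since it is a share of all RT-PCR negatives, and they make large values less likely. Composite 2 offers no remedy for active infection, because it reconsiders RT-PCR positives and does not undo a relabelled negative.

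**Conclusion.** The point holds in conditional form. As written, day-28 IgG alone can make an uninfected, vaccinated adult a missed infection, and no exception prevents it. If v is above zero, enhanced sensitivity against composite 1 is biased downwards. With perfect RT-PCR it is about 76% at v = 1% and 47% at v = 5% for 5% prevalence, and 88% and 81% for 30% prevalence. If composite 1 also recovers true RT-PCR misses, the 5% prevalence figures become about 78–84% and 51–66%. If no one is vaccinated, or the assay does not detect vaccine antibody, the effect is zero.

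It would go too far to say that enhanced sensitivity will collapse, since neither uptake nor assay antigen is documented. It would also go too far to say that the main result is at risk: the primary comparison uses RT-PCR without antibody data. A reader might further infer that good tests will be dropped, because at 5% prevalence and v = 1% false negatives rise from 6 to about 17 against a limit of seven. That would need the stopping criteria to be applied to composite 1. The article suspends them for the first POCTs and leaves open whether the composite can be built quickly enough to use them.

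**What to change.** In Table 4 and its interpretation, add that day-28 IgG is not used to relabel a participant with a COVID-19 vaccination recorded before that sample, in the eCRF or the linked health record, unless the assay targets an antigen absent from the vaccine. The subsequent RT-PCR and admission or death criteria continue to apply wherever the current rules use them. For the past-infection analyses, report results by vaccination status before baseline.

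The cost is one data field, if it is not already collected, and about two sentences of rule wording. The downside is that antibody information is lost for vaccinated adults, so some true RT-PCR misses among them will not be recovered. If no participant is vaccinated, the exception has no effect.

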### Baseline assessments

For adults (≥ 16 years old) study visits will follow the same protocol whether current or past COVID-19 is suspected: the analysis will be different. In children (< 16 years), only those with suspected current COVID-19 will be included. In all cases, the baseline visit will involve the POCT(s) under evaluation and the tests for laboratory reference testing (see below). Following consent being provided, the eCRF will then be used to capture study data as detailed in Supplementary Box S1.

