### Data sources

Table 3 outlines which data sources used to address each research question.

**Table 3 Tab3:** Data sources for analysis

Question	Data source					
	eCRF	*POCT index test* for *active* COVID-19	*Laboratory reference test* for *active* COVID-19	*POCT index test* for *past* COVID-19	*Laboratory reference test* for *past* COVID-19	*Composite reference standard*
*Standard* diagnostic accuracy of *active* infection	Yes	Yes—visit 1. Current and past suspects	Yes—visit 1. Current and past suspects	No	No	No
*Enhanced* diagnostic accuracy of *active* infection	Yes	Yes—visit 1. Current and past suspects	Yes—visit 1. Current and past suspects	No	Yes—visit 2. Current and past suspects	Yes
*Standard* diagnostic accuracy of *past* infection	Yes	No	No	Yes—visit 1. Current and past suspects	Yes—visit 1. Current and past suspects	No
*Enhanced* diagnostic accuracy of *past* infection	Yes	Yes—visit 1. Current and past suspects	Yes—visit 1. Current and past suspects	Yes—visit 1. Current and past suspects	Yes—visit 1 and 2. Current and past suspects	Yes

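### Composite reference standard 1 for past infection counts infections that are current at baseline as past, which biases antibody POCT sensitivity downward in that one secondary analysis

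*Protocol article*

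**What the plan says.** All references are to the protocol article.

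- **Rule for past infection** (Composite reference standards, explanation of Table 4). The rule applies to participants with a negative baseline IgG. On that negative result the article says: "it can be considered a false negative if the 28-day IgG test result is positive". A COVID-related admission or death in the 28 days after baseline has the same effect. The sentence sets no RT-PCR condition.
- **Rule for current infection** (same place). For a participant whose RT-PCR is negative, "it can be considered a false negative if the IgG result is positive at 28 days (newly positive or titres have increased", or on a later positive RT-PCR, or on admission or death.
- **Table 4.** The RT-PCR row of the block that minimises false negatives reads "SARS-CoV-2 RT-PCR Negative (FN) N/A Negative N/A", so day-0 RT-PCR is negative in both the current and the past column. Both columns show IgG negative at day 0 and positive at day 28. Both also carry the alternative trigger "Hospital admission or death (within 28 days) citing SARS-CoV-2 as probable cause".
- **Population** (Data sources, Table 3). For enhanced past-infection accuracy, the laboratory antibody entry is "Yes—visit 1 and 2. Current and past suspects".
- **Index test timing** (Baseline assessments). "the baseline visit will involve the POCT(s) under evaluation"; no POCT is scheduled later.
- **Purpose of paired serology** (Composite reference standards). The serial samples are to "allow us to identify antibody changes to discriminate between current and past infection".
- **Use** (Summary statistics of diagnostic accuracy). Each POCT for past infection is tabulated 2 × 2 against the composite reference standards.

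**The concern.** The reference result should describe past-infection status on the day of the POCT. In a person acutely infected on day 0, IgG that is negative then and positive four weeks later is the expected course of a current infection. Admission in the following weeks is not evidence of an earlier infection either. People who need immediate hospitalisation are excluded, so these admissions reflect events after baseline. The main recruitment route brings in patients with symptoms of current COVID-19, so such people will be in the analysis.

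Composite 1 nevertheless moves them to the past-infection positive row. An antibody POCT that rightly found no antibody on day 0 is then scored as having missed a past infection. For these people the composite is a worse reference than the single baseline IgG it is meant to improve. The third secondary objective could understate the sensitivity of a good antibody POCT, and the reader of the 2 × 2 table would have no way to see why.

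**Working it through.** **Step 1: the two rules side by side (Table 4, minimise FN)**

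| | Current infection | Past infection |
|---|---|---|
| Day-0 RT-PCR | negative | negative (table); no condition (text) |
| Day-0 IgG | negative | negative |
| Day-28 IgG | positive | positive |
| Alternative trigger | admission or death within 28 days | admission or death within 28 days |

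A participant with this pattern is positive on both composites. The text for past infection drops the RT-PCR cell. Even under the table, it is unclear whether that cell also limits the admission route.

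**Step 2: size.** The article states no figure for this bias, so there is none to reproduce. Let

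- q = share with true past infection, all taken as reference-positive;
- p = current prevalence;
- m = share of current infections eligible for relabelling: the RT-PCR false-negative rate under Table 4, 1 under the text;
- c = share of current infections that are IgG-negative at day 0 and positive at day 28;
- a = (1 − q) × p × m × c = share relabelled as past.

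Apparent sensitivity = [q × Se + a × (1 − Sp)] / (q + a).

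*From the article:* p = 5% and 30%, with Se = 90% and Sp = 99% (Stopping criteria, where they are indicative for an active-infection POCT and are borrowed here); RT-PCR false-negative rate 18% to 58% (Composite reference standards). *Assumed:* q = 5%, 10%, 20%; c = 50%, 90%. The admission route is not added.

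| Scenario | a under Table 4 | Apparent sensitivity, Table 4 | Text, m = 1 |
|---|---|---|---|
| Mildest: p 5%, q 20%, RT-PCR FN 18%, c 50% | 0.80 × 0.05 × 0.18 × 0.5 = 0.0036 | (0.1800 + 0.00004)/0.2036 = 88% | 82% |
| Middle: p 30%, q 10%, RT-PCR FN 18%, c 90% | 0.90 × 0.30 × 0.18 × 0.9 = 0.0437 | (0.0900 + 0.0004)/0.1437 = 63% | 27% |
| Most severe: p 30%, q 5%, RT-PCR FN 58%, c 90% | 0.95 × 0.30 × 0.58 × 0.9 = 0.1488 | (0.0450 + 0.0015)/0.1988 = 23% | 16% |

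Over all 24 combinations under Table 4, 20 lose at least 5 percentage points and 16 lose at least 10. Without the relabelling a = 0, and apparent sensitivity is 90% throughout.

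**Step 3: current cases already IgG-positive at baseline.** Step 2 leaves them out, yet they are reference-positive and the POCT should detect them. As an upper bound, let every current infection outside c be of this kind: b = (1 − q) × p × (1 − c), detected at 90%. Apparent sensitivity = [(q + b) × Se + a × (1 − Sp)] / (q + b + a).

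- Mildest: b = 0.80 × 0.05 × 0.5 = 0.0200; (0.1980 + 0.00004)/0.2236 = 89%.
- Middle: b = 0.90 × 0.30 × 0.1 = 0.0270; (0.1143 + 0.0004)/0.1707 = 67%.
- Most severe: b = 0.95 × 0.30 × 0.1 = 0.0285; (0.0707 + 0.0015)/0.2273 = 32%.

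The loss shrinks but remains. Under this bound 19 of the 24 combinations still lose at least 5 points and 14 at least 10.

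**The case against.** **The text should be read with its table.** The article introduces the text as an interpretation of Table 4's cells, and Table 4 shows RT-PCR negative. A reader of the text alone might infer that every RT-PCR-positive acute case who seroconverts becomes a past infection. The documents do not support that as the settled rule. The figures without an RT-PCR condition show what following the text literally would cost. This part is a mismatch to reconcile.

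**The rules are provisional.** Table 4 is framed as potential and hypothetical, and a SAP will hold the details. But the analysis section commits to 2 × 2 tables against these composites, and the article gives no other rule for past infection.

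**Composite 1 is the deliberately inclusive one of a pair.** This is true, and it limits the reach. Composite 2 for past infection acts only on positive baseline IgG, so it does not relabel these people. For the same reason it does not undo what composite 1 does. A reader might infer that the whole third secondary objective gives a wrong answer, but only one of its two composite estimates carries this bias.

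**The pattern is ambiguous.** An RT-PCR-negative seroconverter may have a PCR-missed current infection or a recent past infection with late antibodies. Capturing the latter is the rule's purpose, and two separate tables may each count an ambiguous case. So double labelling is not an error in itself, and only the current-infection part of the reclassification is bias. But the rule has no means of telling the two apart, which is what the paired samples are said to provide.

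**The article has a caveat.** It covers infection acquired between the index test and day 28. It does not cover infection already current at baseline.

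**Conclusion.** The point holds for composite reference standard 1 for past infection. The direction follows from the written rule: whenever current infections seroconvert or lead to admission after baseline, a sound antibody POCT's apparent sensitivity falls. The primary objective, the standard past-infection analysis and composite 2 are not affected by this rule.

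The size is not fixed by the documents. With Table 4's RT-PCR-negative condition, a true 90% appears as about 88% down to about 23% across the scenarios, and lower if the text is followed without that condition. These figures rest on assumed past-infection prevalence and seroconversion share, and on accuracy figures borrowed from an active-infection example. Counting current cases already IgG-positive at baseline moves the most severe figure to at most about 32%. The loss is small when current prevalence is low, past infection is common and few infections are missed by RT-PCR. For scale, the article's example of a minimum acceptable sensitivity is 80%. A POCT with a true 90% falls below it in 16 of the 24 Table 4 combinations, or in 14 with the baseline-positive cases counted.

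**What to change.** 1. Carry Table 4's RT-PCR-negative condition into the text for past infection, so that table and text state one rule.
2. Remove post-baseline admission or death as a trigger for past infection. Keep it for current infection only.
3. Count day-0 to day-28 seroconversion as past infection only where evidence already collected places the infection before baseline: a linked earlier positive RT-PCR or COVID admission, or symptom onset earlier than a pre-specified interval. Keep day-28 IgG positivity as a requirement for the symptom-onset route. The qualifying symptoms are common and non-specific, and onset date alone would turn people who were never infected into past positives. Assign all other seroconversion to current infection.
4. Report a sensitivity analysis that excludes seroconverters whose timing is ambiguous.

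The cost is protocol and SAP wording; symptom duration and linked records are already part of the study. The downside is that fewer baseline IgG-negatives are reclassified, and some late-antibody past infections without dated evidence will be missed.
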